### Sample size estimation

Sample size is estimated based on the primary outcomes, specifically, changes in family members’ stress. In this study, effect size of family members’ stress reduction is anticipated to be medium at 0.50. It is estimated that a sample size of 128 participants (64 per group) will provide this study with 80% power at 5% level of significance (two-tailed). Attrition rates in previous studies ranged from 0% [21] to 34.3% [34], most of which were less than or around 15% [16–18, 20]. In consideration of 15% attrition rate, sample size of this study is finally estimated to be 150 family members (75 per group).

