### Intervention group

Participants in the intervention group will receive a six-session group-based (6 to 10 participants) online education intervention. The intervention will be delivered on a weekly basis, approximately 60 min per week. Participatory approaches (e.g. experience sharing, brainstorm) will be used during the intervention delivery. Participants will be encouraged to complete the whole intervention through text message reminders; yet the situation that participants discontinue the allocated intervention because their relative with dementia dies or moves out of the studied facilities will be allowed.

Session 1 aims to facilitate the participants to reappraise the situations they are facing with, through improving their understanding of dementia. Specifically, the researcher will provide the participants with basic dementia knowledge especially its progression and manifestations at different stages. These kinds of information are anticipated to reduce the participants’ uncertainty about dementia, which may further facilitate the participants to reappraise the situations they are facing with.

Session 2 aims to help the participants manage negative emotions after residential care placement. Firstly, the participants will be encouraged to share their experiences of managing negative emotions after residential care placement. The researcher will introduce the participants some emotion management strategies (e.g. accepting the reality, benefit finding, and humour). In particular, the researcher will guide the participants to find benefits of residential care placement in order to help them reframe stressful situations by wresting positive values form adversity.

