### Data management and analysis

Data will be double entered and checked in EpiData 3.1 (The EpiData Association, Odense, Denmark) and will then be exported to Statistical Package for the Social Sciences (SPSS) version 25.0 (IBM Corporation, Armonk, New York, USA) for analyses. The distribution normality of the continuous variables will be tested by One-Sample Kolmogorov-Smirnov test. The baseline homogeneity between the intervention group and the control group will be tested using the Student’s T test, Mann-Whitney U test, Chi-square test, and Fisher’s exact test, where appropriate. All outcome measures will be compared within and between groups. The generalised estimating equation (GEE) model will be utilised to analyse the intervention effects, with controlling for confounding factors such as the family members’ age, gender, educational attainment, and relationship with the residents, and the residents’ age, gender, educational attainment, type of dementia, and length of stay in the facility. The analyses will be performed based on the intention-to-treat (ITT) principle. For ITT analysis, missing data will be dealt by using the last observation carried forward method, whereby the last available measurement for each participant at the time point prior to withdrawal from the study is retained in the analysis [47]. Statistical significance will be set at *p* < 0.05; all tests will be two-tailed.

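### Last observation carried forward is the only missing-data method for the intention-to-treat analysis, and it biases the stress effect in a direction that depends on when participants are lost

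*Protocol article*

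**What the plan says.** In the protocol article, Data management and analysis states the principle, "The analyses will be performed based on the intention-to-treat (ITT) principle", and the model, "The generalised estimating equation (GEE) model will be utilised to analyse the intervention effects", with covariate adjustment. For missing values, "missing data will be dealt by using the last observation carried forward method", which the article explains as meaning that "the last available measurement for each participant at the time point prior to withdrawal from the study is retained in the analysis". No outcome is exempted and no sensitivity analysis is named.

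Two other sections bear on how much this matters. Sample size estimation allows for attrition ("In consideration of 15% attrition rate, sample size of this study is finally estimated to be 150 family members (75 per group") and cites earlier studies with attrition from 0% to 34.3%. Intervention group anticipates one reason for stopping: the situation that "participants discontinue the allocated intervention because their relative with dementia dies or moves out of the studied facilities will be allowed".

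Outcome measures sets three assessments: t0, t1 and t2.

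**The concern.** LOCF assumes that a score stays where it was last seen. With one baseline and two follow-ups, that is a strong assumption. A family member lost before t1 enters both follow-up comparisons as someone whose stress did not change, and one lost after t1 enters t2 as someone whose t1 response persisted exactly. Neither follows from being randomised, so keeping all 150 in the data set does not by itself estimate the effect in all 150.

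Stress is the outcome on which the trial is sized, and the Discussion says that beneficial results would lead to dissemination to more facilities. At stake are the size of the reported effect, the interval around it and, if loss differs between arms while scores drift, the false-positive rate. Only one arm attends six weekly sessions, so equal loss cannot be taken for granted.

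**Working it through.** **Inputs from the protocol.** The planned effect is "effect size of family members’ stress reduction is anticipated to be medium at 0.50"; the base size is "a sample size of 128 participants (64 per group) will provide this study with 80% power at 5% level of significance (two-tailed"); the attrition allowance is 15%, giving 75 per arm; the highest cited attrition is 34.3%.

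**Assumptions, not in the protocol.** Baseline-follow-up correlation 0.5; loss at random; the split of loss between arms; the control-arm change c. The simulations use one follow-up visit and ordinary regression, which simplifies the planned GEE.

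**1. The plan's own figure.** A two-sided t-test at 5% with an effect of 0.50 needs 63.8, so 64 per group (power 0.801). Inflation gives 128 / 0.85 = 150.6. The stated 128 and 150 reproduce. About 150 × 0.85 = 127.5 participants are expected to be observed.

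**2. Loss before t1.** Let dI and dC be the shares lost in the intervention and control arms. In SD units, with negative meaning less stress:

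LOCF difference = (1 − dI)(c − 0.50) − (1 − dC)c

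- Equal 15% loss: 0.85 × (−0.50) = −0.425 for any c, 15% too small.
- Equal 34.3% loss: 0.657 × (−0.50) = −0.329.
- 20% intervention, 10% control, c = −0.25: 0.80 × (−0.75) − 0.90 × (−0.25) = −0.375.
- 10% intervention, 20% control, c = −0.50: 0.90 × (−1.00) − 0.80 × (−0.50) = −0.500, no bias.

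**3. Interval and power (simulation, baseline-adjusted, 75 per arm).**

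| Equal loss before t1 | LOCF estimate | LOCF coverage of 95% interval | Observed-data estimate |
|---|---|---|---|
| 15% | about 0.43 | about 92% | 0.50 (coverage about 95%) |
| 34% | about 0.33 | about 72% | 0.50 |

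At 15% loss the LOCF standard error is 0.135 against 0.154 on observed data (0.135 / 0.154 = 0.88, about 12% smaller). An analytic check on coverage: the shift is 0.075 and 0.075 / 0.135 = 0.56 standard errors, so coverage is Φ(1.96 − 0.56) − Φ(−1.96 − 0.56), about 91%, in line with the simulation.

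Power at 15% loss, LOCF against observed data with the same model on both sides: baseline-adjusted 88% v 90%; post score 73% v 80%.

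**4. Loss after t1.** Suppose the effect wanes from 0.50 SD at t1 to 0.25 SD at t2, controls are stable, and 15% of the intervention arm is lost in between. LOCF gives 0.85 × 0.25 + 0.15 × 0.50 = 0.2875, about 0.29 against a true 0.25, which is 15% too large. With stable controls, equal loss in both arms gives the same result.

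**5. No true effect.** The formula becomes (dC − dI)c.

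- Equal loss: 0, and simulated type I error stays near 5%.
- Both arms improving by 0.4 SD, loss 20%/10% (intervention/control): (0.10 − 0.20) × (−0.4) = 0.04 SD; type I error about 6%.
- The same drift, loss 25%/5%: (0.05 − 0.25) × (−0.4) = 0.08 SD; type I error 7% to 9%, depending on the model.

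With improvement in both arms and more loss in the intervention arm, the false difference runs against the intervention. If both arms worsened, it would favour it.

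**The case against.** The best defence is that LOCF is mild here. With equal early loss it shrinks a true effect, leaves type I error near 5% and costs about 2 points of power on a baseline-adjusted analysis. That is correct as far as it goes. It does not cover loss after t1 or unequal loss with drift, and shrinkage is still bias, so LOCF cannot be relied on as conservative.

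Four stronger readings are tempting and are not supported:

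- A reader might infer a large loss of power, for instance 72% against 89%. That sets an unadjusted LOCF analysis beside a baseline-adjusted analysis of observed data; most of the gap is the baseline adjustment.
- A reader might infer that the LOCF standard error is miscalculated. In the simulations it matched the spread of the LOCF estimate (both 0.135). The interval fails because it is centred on the wrong value and is narrower than the observed data support.
- A reader might infer that the effect is always diluted, or that false positives are generally inflated. Direction depends on timing and balance, and the protocol gives no split of loss by arm or visit.
- A reader might infer that the plan sets out to invent scores for residents who have died or moved. Intervention group speaks of stopping the intervention, while the carry-forward rule refers to withdrawal from the study, so the link is an inference. Residents with a projected life expectancy of six months or less are excluded and the course is about 12 weeks (six weekly sessions, then six weeks), so deaths should be limited. After a move, caregiving burden and involvement can still be measured.

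**Conclusion.** The point holds as a badly fixed method, not as an omission. The article names LOCF outright, as the sole missing-data rule for every outcome, so a separate analysis plan could not supply what is wrong with it.

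Under the stated assumptions, the stress effect is understated by 15% at the protocol's own attrition allowance and by about a third at its highest cited rate, with interval coverage falling from about 95% to about 92% and about 72%. Loss after t1 can push the other way. The type I error figures depend on unequal splits that the protocol does not give.

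The consequence for resident outcomes is conditional. If participants leave the study when the resident dies, the rule as written would fill in NPI-Q, visiting and personal-care values that do not exist. The case on stress does not depend on this.

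**What to change.** In Data management and analysis:

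1. Delete LOCF as the main method.
2. Analyse all randomised participants with all observed t0, t1 and t2 data in a likelihood-based repeated-measures mixed model (SPSS MIXED). Alternatively, use multiple imputation that includes baseline, arm and the planned covariates, followed by the planned GEE. Simply dropping LOCF and running unweighted GEE on the observed data is not enough, because that needs data missing completely at random.
3. State that family-member outcomes continue to be collected after sessions stop or the resident moves. Restricting burden or involvement to residents still in the facility would discard data that can be collected and would condition on an event after randomisation.
4. State that NPI-Q and involvement outcomes are not imputed after a resident's death, and report deaths and moves by arm.
5. Add one delta-shift sensitivity analysis for data missing not at random.

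The cost is rewording and a little more analysis work in the same software. The sample size and visits do not change, and recruitment was still under way when the article was written.

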## Discussion

Family members usually face challenges and stressors after institutionalising a relative with dementia, this study will evaluate an online education intervention for Chinese family members of residential care facility residents with dementia. This will have implications for nursing research and practice. Firstly, with a mixed methods experimental study design, an online education intervention has been developed based on the Chinese family members’ own perceptions and expectations after placing a relative with dementia into a residential care facility. This will provide evidence to health care professionals and researchers in designing and implementing more successful interventions for this group of population. Secondly, interventions to family members that aim to address their stressors may influence the extent they involve in their relative’s care and thus indirectly affect resident outcomes. This study will shed insight on the effectiveness of an education intervention in terms of both family members and residents with dementia. Thirdly, this study will be of great significance in promoting the implementation of family-centred care in practice especially in residential care, and improving family involvement in their relative’s care after residential care placement.

The results of this study will be presented at national and/or international conferences. Findings pertaining to this study will be submitted and published in peer reviewed scientific journals. If the results of this study demonstrated beneficial effects, the intervention will be disseminated to more local residential care facilities.

## Data Availability

The datasets and any materials used and/or analysed during the current study will be available from the corresponding author on reasonable request.

## Abbreviations

BPSD: Behavioural and Psychological Symptoms of Dementia
FVEP: Family Visit Education Programme
PIC: Partners in Caregiving
CGMI: Chronic Grief Management Intervention
FITT-NH: Family Intervention: Telephone Tracking-Nursing Home
RCTM: Residential Care Transition Module
RCT: Randomised Controlled Trial
PSS: Perceived Stress Scale
BCS: Brief COPE Scale
ZBI: Zarit Burden Interview
NPI-Q: Neuropsychiatric Inventory-Questionnaire
SPSS: Statistical Package for the Social Sciences
GEE: Generalised Estimating Equation
ITT: Intention-to-treat
